# Single-session dialectical behavior therapy skills training versus relaxation training for non-treatment-engaged suicidal adults: a randomized controlled trial

**DOI:** 10.1186/s40359-016-0117-4

**Published:** 2016-03-24

**Keywords:** Dialectical behavior therapy, Treatment engagement, Treatment-seeking, Suicide, Randomized trial, Brief interventions

## Abstract

**Background:**

Individuals who are not engaged in treatment are commonly overlooked in the design of intervention trials targeting suicidal populations as a result of recruitment methodology that requires individuals to be referred from their current provider. In fact, research suggests that the majority of individuals who die by suicide have not been in contact with mental health services in the year before their death.

**Methods/design:**

A randomized controlled trial of two brief, one-session interventions for adults who are not engaged in mental health treatment. Inclusion criteria include 1) 18 years or older, 2) experiencing suicidal ideation in the past week, 3) have not received mental health treatment in the month prior to screening, 4) living within commuting distance to the research office, and 5) willing to consent to recording and assessment. Exclusion criteria are 1) non-English speaking and 2) significant cognitive impairment. Recruitment takes place in the community via flyers, radio, and online advertisements. Interested individuals are screened via telephone and those who are eligible attend a one-time in-person assessment and intervention appointment. During this appointment, they are randomized to a single-session intervention in which they are presented with either dialectical behavior therapy skills or supportive discussion and instruction in relaxation. Following the in-person appointment, participants complete three follow-up interviews via telephone at one-week, four-weeks, and twelve-weeks post-intervention. The primary outcomes are suicidal ideation, emotion dysregulation, and skills use. Secondary outcomes include depression, anxiety, self-efficacy, and treatment utilization. Exploratory outcomes are suicidal and intentionally self-injurious behaviors. Intent-to-treat analyses will be conducted on primary and secondary outcomes.

**Discussion:**

Suicidal individuals who are not engaged in mental health treatment are an understudied and significantly at-risk group for death by suicide. A better understanding of this population, targeted efforts to recruit and engage these individuals, and developing effective interventions for this group are critical areas for investigation in the field that this trial seeks to address.

**Trial registration:**

Clinicaltrials.gov identifier: NCT02236325; Date of registration: 05-Sept-2014

## Background

Suicide and suicidal behavior are major public health problems with enduring consequences. In 2013, suicide was the 10^th^ leading cause of death in the United States for all ages, and was among the top four causes of death for individuals aged 10 to 44 [1]. Worldwide, it is estimated that 800,000 individuals die by suicide each year [2]. In the United States (U.S.) alone, suicide claimed 41,149 lives in 2013 and costs an estimated $41.2 billion in medical and work-loss expenditures annually [1]. Furthermore, an estimated one million people report making a suicide attempt and more than two million people endorse suicidal thoughts each year in the U.S. [3]. Given the associated stigma with suicidal thoughts and behaviors [4], it is likely that these figures underestimate the scope of suicidal behavior.

While there is indication that some effective interventions for suicidal populations exist (e.g., dialectical behavior therapy [5]), there is a subpopulation that has been traditionally overlooked in this field: individuals who do not seek treatment in times of suicidal crisis. With only very rare exceptions, intervention studies targeting suicidal populations typically require that potential participants receive referrals into the trial from their current mental health providers. While a detailed review of the literature is outside the scope of this paper (see [6–8]), of the 56 studies that were reported in the above review papers, roughly 90 % have used medical or clinical referrals exclusively. This recruitment strategy presumes suicidal individuals who are already receiving mental health treatment comprise a sample that is representative of suicidal individuals as a whole, a point for which there is limited evidence. For example, a comprehensive review of 40 studies that reported rates of contact with mental health services prior to suicide found that in the year prior to death by suicide, only 32 % of individuals had made contact with mental health services, while 77 % of individuals had been in contact with primary care physicians. In the month prior to suicide, 19 % contacted mental health services and approximately 45 % contacted primary care [9]. Men and individuals aged 55 and older have also been shown to have the lowest rates of contact (i.e., 18 % of men and 11 % of adults 55 and older have been in contact with mental health services in the year prior to suicide [9]). These results call into question the assumption that treatment-engaged samples are generalizable to the wider suicidal population. In fact, the majority of individuals who die by suicide do not make contact with mental health services leading up to their death.

Another limiting factor of the existing literature is that many RCTs targeting suicidal samples rely on overly restrictive exclusionary criteria. Of the approximately 50 RCTs that have explicitly examined suicide as an outcome, more than a third excluded individuals at high risk of suicide. High risk of suicide being defined as in need of psychiatric treatment, in need of inpatient hospitalization, have been diagnosed with a mental disorder, and/or needing immediate treatment for suicidality [8]. More research to directly address the generalizability of the samples recruited in previously published trials is needed.

Fundamental to the traditional approach to recruiting participants for trials targeting suicidal populations is the assumption that suicidality is a symptom of a clinical disorder, which presupposes that suicidal individuals have a clinical diagnosis. However, Hamdi and colleagues [10] conducted a retrospective study of all suicides in a catchment area in the United Kingdom and found that those who were not in contact with mental health services in the year prior to their suicide death were less likely to have a mental health diagnosis or to report a history of previous self-harm. Additionally, Rhodes and colleagues [11] found higher rates of mental health contact for Canadian individuals experiencing depression and suicidal ideation (61.6 %) and depression alone (50.8 %) than for those experiencing suicidal ideation alone (26.8 %). Among Americans, an estimated 5.2 million adults who needed mental health treatment did not receive any mental health treatment in the past year [12]. Of adults who attempted suicide in the past year, only an estimated 67.2 % (752,000) received medical attention following the suicide attempt [12], indicating that there is a sizeable suicidal population that needs, but is not receiving mental health treatment, and thus not receiving a clinical diagnosis. This evidence suggests that relying on a documented diagnosis or the presence of symptoms that reach a diagnostic threshold may be misguided criteria to use in identifying and initiating intervention with individuals in need of mental health services.

Given the lack of targeted recruitment and outreach to individuals who are not already engaged in mental health treatment or in intervention research, the aim of this randomized controlled trial (RCT) is to evaluate the effectiveness of the brief, one-time, Dialectical Behavior Therapy Brief Suicide Intervention (DBT-BSI, [13]) for currently suicidal individuals who are not already engaged in mental health treatment. This intervention is compared to a relaxation intervention designed to control for non-specific factors.

## Methods/Design

In addition to evaluating the safety and feasibility of delivering this intervention to suicidal individuals who are not otherwise engaged in mental health treatment, this RCT’s aim is to estimate the immediate (one-week) and long-term (four- and 12-week) degree of change and variability of response to the DBT-BSI relative to a relaxation training (RT) control on the primary outcomes of suicidal ideation, emotion dysregulation, and skills use. Secondary outcomes of depression, anxiety, self-efficacy, and treatment utilization are also examined. Specifically, we hypothesize that, relative to the RT control condition:DBT-BSI will result in lower levels of suicidal ideation and emotion regulation;DBT-BSI will result in higher levels of skills use, in general, and in greater use of the specific skills taught in the DBT-BSI;DBT-BSI will result in lower levels of depression and anxiety; andDBT-BSI will result in greater utilization of mental health resources during the follow-up period.

### Participants

Participants were recruited from the community in the northwestern United States using radio, newspaper, community bulletin boards, and online advertisements. Advertisements ask individuals who are currently suicidal to contact the study researchers. This recruitment strategy has been successfully used in previous research targeting suicidal individuals [13]. Inclusion criteria include a) 18 years or older, b) experiencing suicidal ideation in the past week, c) having not received mental health treatment in the month prior to screening, d) living within commuting distance to the research office, and e) willing to consent to recording and assessment. Exclusion criteria are a) non-English speaking and b) significant cognitive impairment.

### Ethics and consent

All individuals recruited to the study underwent a process of informed consent during the initial phone screening assessment. Then, when participants arrived for their in-person appointment, they again underwent an informed consent procedure where they had a second opportunity to ask their study therapist questions before signing an agreement of informed consent. In addition to passing the National Institute of Mental Health ethics review, the study has been approved by the Human Subjects Division of the Institutional Review Board at the University of Washington. Any study modifications were approved by the University of Washington Institutional Review Board and, when appropriate, the National Institute of Mental Health.

Furthermore, a Data and Safety Monitoring Board (DSMB) was convened and a data and safety monitoring plan was developed to be sure that the study was conducted with the utmost conscientiousness. The Data and Safety Monitoring Plan indicated that the trial would be stopped if the majority of participants in either intervention condition exhibited significant and reliable worsening of suicidal ideation, suicidal, and/or self-injurious behavior. The DSMB met biannually to review trial progress and discuss any issues related to participants’ safety, adverse events, or the conduct of the trial.

### Confidentiality

Identifiable data (e.g., participants’ names, phone numbers) were maintained separately from their study data. Upon completion of data collection, identifiable information was destroyed. Non-identifiable data is coded for each participant using a unique, randomly-generated study identification number. This data is stored on a secure, encrypted server that is password-protected, to which only relevant study personnel have access. Additionally, a Certificate of Confidentiality was obtained from the National Institute of Mental Health to ensure an additional level of privacy protection for participants in the event of outside legal requests for identifying information.

### Procedure

Interested individuals who contacted the research office underwent an initial phone screening interview (T0) to determine study eligibility. Those who were eligible for the study were scheduled for on-site baseline assessment (T1) and intervention procedures. Following this in-person assessment and intervention appointment, participants completed three telephone follow-up interviews at 1- (T2), 4- (T3), and 12- (T4) weeks. Assessment domains include cognitive impairment (6-Item Cognitive Impairment Test) [14], suicidal ideation (Scale for Suicidal Ideation) [15] and suicidal behaviors (Lifetime Parasuicide Count) [16], emotion dysregulation (Difficulties in Emotion Regulation Scale) [17], depression (Patient Health Questionnaire Depression Module) [18], anxiety (Beck Anxiety Inventory) [19], skills use (DBT Ways of Coping Checklist) [20], and treatment utilization (Treatment History Interview; Linehan & Heard, unpublished work). Additionally, measures to prompt assessment and documentation of suicide risk were included (University of Washington Risk Assessment Protocol and the University of Washington Risk Assessment and Management Protocol) [21]. Participants were eligible to receive up to $45 in compensation for completing all study assessments (T1 = $5, T2 = $10, T3 = $10, T4 = $20).

The phone screening interview (T0) was conducted by the principal investigator and research assistants under the supervision of the principal investigator. The on-site baseline assessment (T1) and intervention appointments were conducted by three master’s-level graduate students in doctoral psychology programs. Weekly supervision and consultation were utilized for ongoing training and to monitor adherence to the intervention procedures.

### Randomization

A computerized minimization randomization algorithm was used to match participants on three variables that may confound analytic results. These three variables are identified gender, history of suicide attempts, and whether the participant was interested in mental health treatment. Participants were randomized using a 1:1 ratio, such that equal numbers of participants were assigned to each condition. Following completion of the T1 assessment, the therapist entered the participants’ data related to the three potentially confounding variables into the computerized program and participants were randomly allocated to one of the two conditions.

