### Power calculation

A power analysis was conducted prior to the start of the study to provide a guide to sample size requirements. Calculations were based on feasible differences in treatment effect at the three-month follow-up assessment (T4). Based on Cohen’s [28] discussion of effect sizes, the effect size from the pilot study was consulted [13]. The effect size for the decrease in suicidal ideation observed during the pilot study was 0.56, which is considered a medium effect. In order to power the study with a medium effect size for detecting changes in suicidal ideation, the study will require 53 participants per intervention condition, using an independent sample *t*-test between the active and control condition (G*Power) [29].

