### Analyses

Hierarchicial linear modeling [30, 31] will be used to assess differences between conditions over time. The within-subjects model (level-1), will include the estimates of the individual changes in repeated measures of suicide ideation, emotion dysregulation, skills use, depression, and anxiety assessed over time. The between-subjects model (level-2), will incorporate condition assignment as a predictor of the Level-1 growth parameters. Effect sizes will be computed using Feingold’s formula [32] and interpreted using Cohen’s guidelines [28].

Intervention effects for binary outcomes (i.e., use of the skills taught during the intervention, mental health treatment contact, and suicidal behaviors) will be evaluated in much the same way as continuous outcomes. Specifically, an extension of the generalized linear model, the generalized estimating equation (GEE) approach will be used [33, 34]. GEE is an increasingly popular approach to longitudinal and repeated measures designs, especially in the case of binary and categorical outcomes [35] owing to its simplicity relative to mixed models for fitting binary data. Effect sizes will be computed using relative risk ratios [36].

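### Allocation is minimised on three factors, but the analysis as described names condition alone, which risks over-wide standard errors and some lost power if those factors predict outcome

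*Protocol article*

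**What the plan says.** Protocol article, Randomization: allocation was by a minimisation program, in order to "match participants on three variables that may confound analytic results". The section continues: "These three variables are identified gender, history of suicide attempts, and whether the participant was interested in mental health treatment". The ratio is equal ("Participants were randomized using a 1:1 ratio"). The therapist entered the three values into the program after the baseline assessment and before allocation. The section describes the variables as potential confounders a second time at that point.

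Protocol article, Analyses: for the continuous outcomes, hierarchical linear modelling "will be used to assess differences between conditions over time". The section sets the model out level by level. Level 1 holds the repeated measures, and level 2 "will incorporate condition assignment as a predictor of the Level-1 growth parameters". For the binary outcomes (use of the taught skills, treatment contact, suicidal behaviours), "the generalized estimating equation (GEE) approach will be used", with relative risks as the effect measure. No minimisation factor appears in either description, and no covariate is ruled out.

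**The concern.** A variable can confound only if it is related to the outcome, so the article's own description implies that the three factors may be prognostic. Minimisation makes the arms nearly alike on them, so they contribute little to the chance difference between arms. A model without them still treats their variance as noise, as if allocation had been simple randomisation. Its standard error then exceeds the real sampling variability, the test is conservative, and power is lost. A robust GEE standard error does not cure this, because it too takes no account of the balancing.

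The trial has little power to spare. It enrolled 13 fewer than planned and 70 of 93 participants reached the 12-week interview. The article itself concedes inadequate power for small differences (Status of the trial).

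**Working it through.** **Inputs.** From the article: d = 0.56 ("The effect size for the decrease in suicidal ideation observed during the pilot study was 0.56, which is considered a medium effect"), 53 per arm and an independent-samples t-test (Power calculation); N = 106 − 13 = 93 (Status of the trial). Assumed, because they are not stated: two-sided 5% level, 80% power for the planning calculation, and R², the share of outcome variance explained by the three factors.

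**The plan's own figures.** With the noncentral t, d = 0.56 needs 51.03, so 52 per arm, and d = 0.55 needs 52.87, so 53 per arm. The stated 53 is therefore consistent with the pilot effect. At N = 93 the detectable effect at 80% power is d = 0.587, inside the stated 0.5 to 0.6, and power at d = 0.56 is 76.2%. Both stated figures stand.

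**Standard error.** With 46 and 47 per arm and unit variance, the unadjusted SE is √(1/46 + 1/47) = 0.207. Under perfect balance the true SD is 0.207 × √(1 − R²): 0.197 at R² = 0.10 and 0.185 at 0.20. Simulated minimisation gave 0.194 to 0.199 and 0.183 to 0.188.

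**Size and power, two-group comparison.** The simulation used N = 93, three binary factors and 4,000 runs per cell. Each cell shows minimisation with a biased coin of 0.8, then deterministic minimisation, in %.

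| R² | Size, unadjusted | Size, adjusted | Power, unadjusted | Power, adjusted | Loss (points) |
|---|---|---|---|---|---|
| 0 | 4.7 / 5.2 | 4.7 / 5.1 | 76.4 / 76.2 | 76.4 / 76.1 | 0 |
| 0.05 | 4.6 / 4.5 | 5.1 / 5.1 | 77.2 / 75.6 | 79.0 / 77.2 | about 2 |
| 0.10 | 4.3 / 4.2 | 5.1 / 5.1 | 77.3 / 76.8 | 79.9 / 80.1 | about 3 |
| 0.20 | 2.9 / 2.7 | 4.6 / 4.5 | 77.7 / 78.6 | 84.4 / 84.7 | 6 to 7 |
| 0.30 | 2.4 / 2.5 | 5.0 / 5.5 | 79.7 / 80.3 | 89.5 / 89.4 | 9 to 10 |

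Monte Carlo error is about √(0.05 × 0.95/4000) = 0.3 points for size and √(0.77 × 0.23/4000) = 0.7 points for power. As a check, adjusted power from the noncentral t with d/√(1 − R²) is 78.3%, 80.4%, 84.8% and 89.1% at R² = 0.05, 0.10, 0.20 and 0.30.

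**Growth model.** The planned test is on growth parameters, not on one time point. With complete, balanced data the condition-by-time effect is the difference in mean within-person slopes, so anything that shifts only a person's level drops out. This simulation used N = 93, d = 0.56 in slope SDs, allocation balanced within strata and 6,000 runs.

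| Slope variance explained | Size, unadjusted / adjusted (%) | Power, unadjusted / adjusted (%) |
|---|---|---|
| 0 (level only) | 5.0 / 4.9 | 77.4 / 77.3 |
| 0.05 | 5.1 / 5.6 | 77.0 / 78.3 |
| 0.10 | 3.9 / 5.3 | 76.9 / 80.4 |
| 0.20 | 3.1 / 5.1 | 79.2 / 85.3 |

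**Treatment contact.** Entrants had no mental health treatment in the month before screening (Participants), so an effect on contact shows as a difference in follow-up level, and the level-only exemption does not help. To illustrate with assumed figures, let half of participants be interested in treatment.
- Contact risks of 50% and 20%: mean 0.35, R² = 0.15²/(0.35 × 0.65) = 0.10. Under perfect balance the true size is 2 × [1 − Φ(1.96/√0.90)] = 3.9%.
- Contact risks of 60% and 10%: R² = 0.25²/(0.35 × 0.65) = 0.27, and the true size is 2.1%.

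**The case against.** The strongest reply is that the text makes condition a predictor, not the only one. This is a condensed article, and a covariate list is something it may leave to a fuller plan. A reader might infer that adjustment has been ruled out; the article does not say so. What remains is that it describes the model level by level, highlights the three factors at allocation and then drops them. An analyst following it as written would fit an unadjusted model.

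The second reply is that the harm is conditional. A reader might infer that power has certainly been lost, but the article gives no prognostic strength for any factor, and at R² = 0.05 or below the loss is about 2 points or less. This stands. So does the point that single-time-point figures overstate the matter for the slope test when the factors affect level alone.

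Third, data collection has ended, so changing the main model now is a change made after the data were collected. That is fair, though the covariates are dictated by the allocation scheme rather than picked from the results, and the article reports the analysis as still in progress.

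Fourth, three covariates may be too many for suicidal behaviours, an exploratory outcome, if events are few. This also stands, and the fix allows for it.

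**Conclusion.** The point holds in a limited form. Allocation uses three factors that the described analysis does not name. If they predict change in the continuous outcomes, or the level of the binary ones, the unadjusted analysis is conservative. In the two-group comparison the true size of the nominal 5% test is about 4.2 to 4.3% at R² = 0.10 and 2.7 to 2.9% at 0.20, with about 3 and 6 to 7 points of power lost. The direction is secure; the size rests on an assumed R².

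A reader might go further and conclude that the trial's positive findings would be unreliable or its sample size wrong. Neither follows: the error runs towards too few rejections, randomisation still protects against bias, and both 53 per arm and the 0.5 to 0.6 detectable range are consistent with recalculation.

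**What to change.** State in the Analyses section that the three minimisation factors enter as follows, or say why they do not.

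- **Hierarchical models:** fixed level-2 predictors of both intercept and slope, that is, main effects and factor-by-time terms. Main effects alone are not enough for the condition-by-time effect. In a random-intercept-and-slope calculation at the trial's visit times (N = 96, assumed variances, independent intercept and slope, factors explaining 20% of slope variance), its SE was 0.2185 unadjusted and 0.2185 with factors on the intercept only. It fell to 0.1985 once factor-by-time terms were added.
- **GEE for skills use and treatment contact:** the three factors as covariates, with standardised risks so that the reported effect remains a marginal risk ratio.
- **GEE for suicidal behaviours:** reduce or drop the covariates if events are too few, by a rule set in advance on pooled counts.
- **Sensitivity analysis:** the unadjusted models.

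The cost is about six parameters per hierarchical model (3 main effects + 3 factor-by-time terms, with two-level factors and linear time; more otherwise). No new data are needed, since the values were entered before each allocation. Because data collection is over, date and document the change as made before anyone saw results by arm. If that is no longer possible, disclose it and report both analyses.
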